#### Study consent

There are 4 types of consent included in this study protocol. This study involves a time-critical intervention in TBI patients who may be unconscious, unable to consent to participation or no next of keen available within the therapeutic window of the study; therefore, a deferred consent will be obtained for subject’s enrollment in the study and signed by 2 physicians. In this case, the subject will receive the allocated study intervention provided by the treating independent physician and a study team member. Whenever available, the participant’s next-of-kin will be asked to sign consent to continue subject’s participation in the study. Patient who recovers enough cognition to understand the details of the consent will be asked to consent for continuation in the study (delayed informed consent). Patient, who presents with mild injury and can communicate well, will be asked to sign a written formed consent. In all the scenarios, a copy of the consent will be provided and refusal or withdrawal from the study at any time is the patient right and this will not affect his access for full standard of care management. The consent will allow the subject to permit/or decline the use of leftover blood samples to be used for further research.

### Data management

The Trauma Surgery research section at HGH will be responsible for project coordination and data management activity. A pre-designed paper case report form (CRF) will be used as source document to individually record all relevant information regarding the enrolled subjects. Prospective data collection including follow-up assessment (FIM and GOS) will be monitored for accuracy and consistency by the study team members on a regular basis. Complete data will be obtained for all study subjects, including those who fail to continue the BB protocol. The de-identified data from the individual CRF will be entered into a secure password protected computer. After study completion, the CRF, consent form, and data will be stored in accordance with the local regulatory requirements. The PI will provide specific code numbers to each specimen collected and only the project/data manager will know the subject identifier. The investigator will track all the specimens received by allotting unique subject identifier for all blood specimens and track the sample transportation, processing, and consumption. After study finishes, link between code and identifier will be destroyed. The de- identified data will be kept for a period of five years and then will be destroyed.

### Study end points and completion

We expect to complete the targeted subject recruitment and follow-up within 24 months. A subject will be in the research study until 3 months post enrolment or death. Patients will be followed up for Functional Independence Measure (FIM) at the latest time measured and Glasgow Outcome Score (GOS) at 3 months (in the clinic or through telephonic script). Patients and/or their next-of-kin will be asked to provide contact numbers to assess the outcome during follow-up.

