**Fig. 1 Fig1:**
[figure not shown]
BBTBBT protocol

Patients will be stratified based on the admission GCS prior to randomization. Serial electrocardiography (ECG) will be performed for all patients. Patients with abnormal ECG and/or positive troponin will also undergo transthoracic echocardiography, if indicated. Participant timeline is given in Table 1

**Table 1 Tab1:** BBTBBT timeline

Procedure/intervention/task	Day 1	Day 2	Day 3	Day 4	Day 5	Day 6	*Day 10	*Day 30	3-month
Selection criteria^1^	X								
Informed consent	X								
CT scan head^2^	X								
HsTnT^3^	X								
Vital signs^4^	X	X	X	X	X	X			
Randomization	X								
Treatment protocol^5^	X	X	X	X	X	X			
Electrocardiography (ECG)	X	X							
Echocardiography^6^	X								
Laboratory tests (S100B, enolase, cytokines (IL-1b,6,8,18))	X	X	X						
Serum epinephrine	X	X							
Routine blood tests^7^	X								
Glasgow Outcome Score (GOS)									X
Last day follow-up									X

1 = on admission, 2 = on-admission if hemodynamically stable and head injury suspected, 3= within 4 h and to repeat after 6 h, 4= continuous monitoring and to be documented before starting treatment, 5 = beta blocker vs. placebo within the 1st 24 h of admission, 6 = if troponin positive and ECG changes,7 = blood hemoglobin, platelet count, international normalized ratio, prothrombin time, activated partial thromboplastin time, blood glucose level, C-reactive protein, serum creatinine, urea, lactate, base deficit, sodium, and potassium, * = outcome (alive vs. dead)

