### Outcome measures

The primary outcome is to determine whether early administration of propranolol based on the HsTnT status influences the 10- and 30-day mortality in TBI patients.Secondary *endpoints* include the effect of propranolol administration on the duration of hospital stay and functional status, measured using Functional Independence Measure (FIM) score at the latest time and Glasgow Outcome Score (GOS) at 3 months.We will also perform secondary exploratory analyses: (i) to correlate the HsTnT value with the serum S100 calcium binding protein B and enolase (markers of brain injury) value and the injury severity, (ii) to correlate the HsTnT value with the inflammatory markers and *e*pinephrine, and (iii) to examine the association between the HsTnT result and type of TBI lesion based on the CT scan.

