### Statistical analysis plan

The proposed sample size is based on an estimated rate of 12% reduction in mortality with the use of BBs in TBI patients reported by Salim et al. [13], having 80% power and 5% alpha error; the estimated sample size would be 257 subjects (including 5% dropout) in each study group (total 771 patients).

All analysis will be blinded to treatment assignment and will be performed by an independent biostatistician at Hamad Medical Corporation. We will also perform multivariate logistic regression analysis after adjusting for relevant covariates in addition to the differential intervention with an adjusted risk ratio and 95% confidence interval for the probability of death. Analysis will be based on intension-to-treat. Additional exploratory analyses will be performed for continuous variables such as marker of brain injury, injury severity scoring and head Abbreviated Injury Scale, cytokine level by comparing their distributions between intervention arms, and then by multiple linear regression models including other potential covariates of interest. We will explore the effectiveness of the intervention in subgroups using stratified analysis as well as multivariable models. The response to BBs use based on the type of brain lesion will be analyzed. Data analysis will be carried out using the Statistical Package for Social Sciences version 26 (SPSS Inc. USA).

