## Discussion

From the therapeutic point of view, BBs use was reported to have better survival in blunt TBI patients [4, 13, 14, 25, 26, 34–40]; however, double-blind RCTs remain lacking. Despite the optimistic results from prior data, a protocolized early BBs use is not currently a routine practice in patients sustaining TBI. Moreover, the release of cardiac troponin after head injury needs more scientific elaboration and physician awareness. A recent meta-analysis involving 12,721 patients showed that administration of BBs after TBI was associated with a significant reduction in adjusted in-hospital mortality (OR, 0.39) [35]. Retrospectively, Salim et al. [13] reported that patients with severe TBI who did not receive BBs had a mortality rate of 36% vs. 24% in those who received BBs (*p* = 0.036). Furthermore, if troponin-I was elevated on admission, the hospital mortality increased to 48.5% in patients without BBs therapy vs. 22.4% in those who received BBs (*p* = 0.026). In brief, the greatest survival benefit was observed retrospectively in the BBs group based on the conventional troponin positivity on admission.

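### FIM is defined as the last score available, with no fixed assessment time, so survivors can be scored at different times since injury

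*Protocol article*

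**What the plan says.** The rule appears twice in the protocol article. Outcome measures lists as secondary endpoints "the effect of propranolol administration on the duration of hospital stay and functional status", the latter "measured using Functional Independence Measure (FIM) score at the latest time and Glasgow Outcome Score (GOS) at 3 months". Study end points and completion repeats it: "Patients will be followed up for Functional Independence Measure (FIM) at the latest time measured and Glasgow Outcome Score (GOS) at 3 months". That sentence adds that follow-up may be in clinic or by scripted telephone call.

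Table 1 has a GOS row marked at 3 months and a final follow-up row marked at 3 months. It has no row for FIM at any visit, and no section gives FIM a day, visit or window.

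Two further statements bear on how the rule may be read. Data management groups FIM with GOS: "Prospective data collection including follow-up assessment (FIM and GOS) will be monitored for accuracy and consistency". Study end points and completion sets the length of participation: "A subject will be in the research study until 3 months post enrolment or death".

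**The concern.** The point concerns survivors. After brain injury, function changes with time, so a FIM score reflects both how well a patient recovers and when the score was taken. Under a last-available rule, one survivor may contribute a score from the hospital stay and another a score at 3 months. Even if this mixture is the same in both arms, it adds spread that has nothing to do with treatment.

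The date of the last score is also settled after randomisation. Length of stay is a companion secondary endpoint, so the trial itself asks whether propranolol changes it. If last scores cluster around discharge and stay differs between arms, the randomised comparison of FIM (group 2 against group 3) is no longer made at a common time. At stake is the interpretation of one secondary functional endpoint, not the primary result.

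**Working it through.** **The plan's own figures.** The document states no mean, SD, difference or power for FIM, so there is no FIM figure to reproduce. The only sample size is for mortality: 257 per group including 5% dropout, "having 80% power and 5% alpha error", from a retrospective study in which untreated patients "had a mortality rate of 36% vs. 24% in those who received BBs". The sidedness of the test is not stated; two-sided is assumed here.
- Without continuity correction: n = [1.960·√(2·0.30·0.70) + 0.842·√(0.36·0.64 + 0.24·0.76)]² / 0.12² = 227.7, that is 228.
- With continuity correction: (227.7/4)·[1 + √(1 + 4/(227.7·0.12))]² = 244.1, that is 245.
- Dropout: 245/0.95 = 258, or 257 if 244.1 is carried unrounded.

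The stated figure reproduces, but it has no bearing on FIM timing.

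**Timing artefact with identical recovery in both arms.** All inputs from here on are assumptions. Take FIM(t) = 126 − (126 − F0)·exp(−t/τ), score everyone at discharge, and let discharge be unrelated to function. If one arm stays d days fewer than L, its spurious deficit is (126 − F0)·[exp(−(L − d)/τ) − exp(−L/τ)]. Over F0 = 40, 60, 80; τ = 20, 40, 80 days; L = 10, 20 days:

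| Stay shorter by | Smallest deficit | Largest deficit |
|---|---|---|
| 1 day | 0.5 | 2.7 |
| 2 days | 0.9 | 5.5 |
| 4 days | 1.8 | 11.5 |

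The smallest values come from F0 = 80, τ = 80, L = 20. The largest come from F0 = 40, τ = 20, L = 10; for 4 days, 86·(exp(−0.3) − exp(−0.5)) = 11.5.

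**Simulated scenarios.** F0 has mean 60 and SD 15; τ is lognormal with median 40 days and log-SD 0.4; where stay is unrelated to function, it is lognormal with median 15 days and log-SD 0.6.
- A. Same recovery, FIM at discharge, stay shorter by 1, 2 or 4 days: differences of −1.1, −2.2 and −4.6 points (SD about 16). At a fixed 90 days the difference is 0.
- B. Discharge on reaching FIM 100, with one arm truly recovering faster (τ × 0.8): that arm's stay is 7.8 days shorter, the FIM difference at discharge is 0.0, and the difference at 90 days is +3.0. The benefit is hidden.
- C. 70% scored at 90 days and 30% at discharge, independently of arm: difference about 0.
- D. True faster recovery (τ × 0.8), discharge unrelated to function: +3.9 with equal stay, +1.3 with a stay 2 days shorter, −1.4 with a stay 4 days shorter.

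**Variance alone.** Take FIM(t) = 126 − 60·exp(−t/30), between-patient SD 12, and stay with median 8 or 10 days by arm (log-SD 0.7). The mean at discharge is about 83.5 (82.1 and 85.0 by arm) and the score at 90 days is 123.0. If half of each arm is scored at each time:
- between-time variance = (0.5·(123.0 − 83.5))² = 390
- variance from spread in discharge dates = 0.5·(15.4² − 12²) = 47
- total = 144 + 390 + 47 = 581, so the SD is about 24 against 12 at a fixed 90 days.

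That is about four times the variance from mixed timing.

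**The case against.** A reader might infer that the arms will be compared at different points of recovery, and that whichever arm goes home sooner will look functionally worse. The document does not support either statement. Nowhere does it say that the last FIM is the discharge FIM. Data management calls FIM a follow-up assessment alongside GOS, subjects stay in the study to 3 months, and a final contact at 3 months is scheduled. A last FIM taken at that contact is a plausible reading. The direction is not settled either: scenario B shows an earlier-discharged arm looking equal while truly doing better, and scenario C shows no bias. Nor does the document say that propranolol is expected to shorten the stay; it lists the effect on stay as something to examine.

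It is also tempting to quote one alarming probability. With the 60-point curve used for the variance check, every survivor scored at discharge, median stays of 8 and 10 days, and 240 survivors per arm, the spurious difference is 3.0 points (0.19 SD) and the chance of a significant result is 56%. These inputs are one adverse choice. A 1-day difference in stay gives 20%. A starting deficit of 20 points gives 14%, and one of 10 points gives 7%; low deficits are credible because enrolment reaches GCS 15. The survivor count is also high. 257 × 0.95 is about 244, and the 24% to 36% mortality behind the sample size leaves 185 to 156. At 170 per arm the 56% becomes 43%.

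Finally, a condensed article may leave visit windows to a fuller document, and 3-month GOS already gives a functional comparison at a common time. The second part stands and limits the consequence. The first does not remove the point: the article does not omit the timing but states a last-available rule twice, and no later analysis can recover a 3-month score that was never collected. If the full protocol or case report form already schedules FIM at 3 months, only the wording needs to be brought into line.

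**Conclusion.** The point holds as a badly fixed endpoint definition. As written, FIM mixes assessment times that are set after randomisation, while GOS does not. The extra variance follows whenever survivors are scored at different stages of recovery. Bias between arms follows only if last scores often fall near discharge and stay differs by arm, and its sign depends on why patients are discharged.

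The size cannot be derived from the document. On the assumed curves, with identical recovery, FIM at discharge and discharge unrelated to function, a stay 1 to 4 days shorter produces a deficit of about 0.5 to 11.5 points. It is about 0 when timing is unrelated to arm or FIM is taken at 3 months. FIM is secondary; mortality and 3-month GOS are not affected.

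**What to change.** In Outcome measures and in Study end points and completion, define FIM as the score at 3 months, within a stated window, taken at the same clinic visit or telephone contact as GOS. Add a 3-month FIM row to Table 1. Report the last in-hospital FIM descriptively only. Treat a missing 3-month FIM as missing and do not replace it with an earlier score; the earlier score and its date may inform an imputation model.

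The cost is a short amendment and one more instrument at a contact already planned for every survivor. The downside is a somewhat longer 3-month contact and some missing FIM scores that a last-available rule would have filled.

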### Statistical analysis plan

The proposed sample size is based on an estimated rate of 12% reduction in mortality with the use of BBs in TBI patients reported by Salim et al. [13], having 80% power and 5% alpha error; the estimated sample size would be 257 subjects (including 5% dropout) in each study group (total 771 patients).

All analysis will be blinded to treatment assignment and will be performed by an independent biostatistician at Hamad Medical Corporation. We will also perform multivariate logistic regression analysis after adjusting for relevant covariates in addition to the differential intervention with an adjusted risk ratio and 95% confidence interval for the probability of death. Analysis will be based on intension-to-treat. Additional exploratory analyses will be performed for continuous variables such as marker of brain injury, injury severity scoring and head Abbreviated Injury Scale, cytokine level by comparing their distributions between intervention arms, and then by multiple linear regression models including other potential covariates of interest. We will explore the effectiveness of the intervention in subgroups using stratified analysis as well as multivariable models. The response to BBs use based on the type of brain lesion will be analyzed. Data analysis will be carried out using the Statistical Package for Social Sciences version 26 (SPSS Inc. USA).

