Earlier studies have focused primarily on the clinical relevance of the conventional troponin T (TnT) or I (TnI) in patients with critical illness but did not examine well the newer high-sensitive TnT (HsTnT) which has a higher sensitivity and shorter time to detect minor myocardial damage [9]. An earlier study reported a higher rate of mortality in patients with elevated serum troponin levels as compared to normal troponin in isolated TBI patients [17]. The high-sensitive troponin I was tested in patients with mild TBI, and authors [18] have reported a significant association between positive HsTnI and the abnormal head CT scan findings as compared to a negative CT scan in those with negative HsTnI. A recent meta-analysis [19] reported that among TBI patients, the effect of elevated troponin on mortality had a pooled odds ratio (OR) of 3.3, which is almost like that reported in non-traumatic brain injuries studies.

A recent study from our center revealed an all-cause mortality of 26% in TBI patients and the mortality rate was 4-fold higher in those who presented with elevated HsTnT levels [20]. In this study, positive HsTnT was reported in 65% of patients with moderate to severe TBI. Moreover, on multivariate regression analysis, positive HsTnT was an independent predictor of in-hospital mortality even after adjusting for any chest trauma [20]. Myocardial injury, defined as at least single cardiac troponin concentration above the 99th percentile upper reference limit, has been reported following TBI with a likely dose-response relationship with the severity of the head injury [21]. In patients with isolated TBI, a recent study found significant correlations between the on-admission TnI value and Glasgow Coma Scale (GCS), head Abbreviated Injury Scale (AIS), and Acute Physiology and Chronic Health Evaluation II score (APACHE II) [22].

Beta-adrenergic receptor blockers (BBs) may reduce the cascade of immune and inflammatory changes associated with injury as well as the heart rate and blood pressure. Blunting the beta-adrenergic sympathetic surge using BBs has been shown to reduce mortality post-trauma and post non-cardiac surgery in several studies [8, 16, 23–25]. Early administration of propranolol was found to be independently associated with lower mortality among patients with moderate to severe TBI (adjusted odds ratio, 0.25) and having a better functional outcome (GOS-E) at 6-month follow-up [25, 26].

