### Study rationale

To date, no randomized controlled trial (RCT) has focused on the early administration of BBs in TBI patients based on the HsTnT status. BBs administration is still not the standard of care for TBI patients. However, prior observational studies have suggested that early low-dose propranolol can be safely administered and might improve outcomes after TBI [25, 27, 28] or severe trauma [29]. According to a recent meta-analysis [30], there is a single RCT that assessed the potential adverse events associated with BB therapy in TBI. There was no significant difference between the study groups in terms of the incidence of hypotension, bradycardia, heart failure, and bronchospasm.

The question of whether early administration of BBs has beneficial effect on the 10- and 30-day mortality in patients with mild-to-severe TBI based on the admission HsTnT status will be investigated in this study. Of note, there are various questions that need exploration such as (a) whether the severity of head injury alone or in combination with biomarkers will be a guide for the early use of BBs in TBI, (b) whether these biomarkers reflect the sympathetic surge only or the silent myocardial injury as well, and (c) whether these biomarkers have prognostic value only or they also possess diagnostic and therapeutic implications in TBI. To address this gap in the literature, we are undertaking a large double-blind RCT comparing protocolized, early administration of propranolol (within the first 24 h of hospital admission and after the HsTnT result) in the management of TBI patients. This study will be powered sufficiently to detect clinically relevant differences in all-cause mortality and neurological outcomes.

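### The 80% power behind 257 per group is not supported for the only randomised comparison, because the assumed 36% and 24% mortality come from a different population

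*Protocol article*

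**What the plan says.** The Statistical analysis plan section of the protocol article gives the basis of the sample size: "The proposed sample size is based on an estimated rate of 12% reduction in mortality with the use of BBs in TBI patients". It specifies "having 80% power and 5% alpha error" and arrives at "257 subjects (including 5% dropout) in each study group (total 771 patients"). The underlying rates are in the Discussion, which cites the same retrospective study: "patients with severe TBI who did not receive BBs had a mortality rate of 36% vs. 24% in those who received BBs". For patients in that study with elevated troponin, "the hospital mortality increased to 48.5% in patients without BBs therapy vs. 22.4% in those who received BBs".

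The sections Participants and study setting, Randomization and Discussion agree on who is randomised. HsTnT-positive patients without a contraindication all receive propranolol (group 1). HsTnT-negative patients are allocated 1:1 to propranolol (group 2) or placebo (group 3). Eligibility covers mild to severe injury (head AIS 1-5 and/or GCS 4-15).

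The Introduction reports the centre's own experience: 26% all-cause mortality in TBI, "the mortality rate was 4-fold higher in those who presented with elevated HsTnT levels", and "positive HsTnT was reported in 65% of patients with moderate to severe TBI".

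The Study rationale states: "This study will be powered sufficiently to detect clinically relevant differences in all-cause mortality and neurological outcomes".

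**The concern.** Group 2 against group 3 is the only comparison protected by randomisation, so the primary mortality hypothesis depends on it. The rates used for sizing differ from that population in two ways, and both point to lower mortality among those randomised. The source cohort had severe TBI, whereas this trial includes mild TBI. The source cohort was not restricted by troponin, whereas this trial randomises only troponin-negative patients, whom the centre's own data show to be at much lower risk. The Discussion adds that the largest survival difference was seen in troponin-positive patients, the stratum that is not randomised.

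The group sizes raise a second problem. Membership of group 1 is decided by a test result, yet 771 is divided into three equal groups. Participants and study setting gives the recruitment target as 771 in total, and the interim looks (n = 193 and n = 386) are 25% and 50% of that total. A total of 771 enrolled does not by itself secure 514 randomised.

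At stake is how a non-significant mortality result will be read. If the trial is described as adequately powered when it is not, such a result may be taken as evidence that propranolol has no effect.

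**Working it through.** **1. The plan's own figure.** Inputs: 36% and 24% (Discussion); 80% power, 5% alpha and 5% dropout (Statistical analysis plan). Two-sided testing is assumed, because the sidedness is not stated.

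- Uncorrected: n = [1.960·√(2·0.30·0.70) + 0.842·√(0.36·0.64 + 0.24·0.76)]² / 0.12² = 227.7 per group.
- Continuity-corrected: n' = (n/4)·[1 + √(1 + 4/(n·0.12))]² = 244.1.
- Dropout: 244.1/0.95 = 257.0.

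The 257 reproduces. It leaves 257 × 0.95 = 244 evaluable per arm.

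**2. Mortality in HsTnT-negative patients.** The protocol does not state this, so it is derived from the Introduction. Let m be the risk in negatives, 4m the risk in positives (4-fold read as a ratio of 4), and f the share positive. Then 0.26 = f·4m + (1 − f)·m, so m = 0.26/(1 + 3f).

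- f = 65% (the reported share): 0.26/2.95 = 8.8%
- f = 50% (assumed): 10.4%
- f = 33% (assumed): 13.0%
- f = 20% (assumed): 16.3%

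A 12-point absolute reduction is impossible below 12% control risk. At 13% it would mean 13% falling to 1%.

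**3. Power with 244 evaluable per arm.** Formula: power = Φ[(d − 1.960·SE₀)/SE₁], with d the risk difference, SE₀ the pooled standard error and SE₁ the unpooled one. There is no continuity correction, which favours the plan: on this formula 36% against 24% gives 83%.

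Worked case: the source's relative risk is 24/36 = 0.667, so 8.8% becomes 5.87%. Then d = 0.0293, SE₀ = 0.0236, SE₁ = 0.0236, and (0.0293 − 0.0463)/0.0236 = −0.72. Power is 24%.

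| Control risk | RR 0.667 (sizing source) | OR 0.39 (meta-analysis, Discussion) | OR 0.25 (early propranolol, Introduction) |
|---|---|---|---|
| 5% | 15% | 43% | 65% |
| 8.8% | 24% | 66% | 88% |
| 13% | 34% | 82% | 97% |
| 26% | 64% | 98% | >99% |

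At 8.8% and relative risk 0.667, 80% power would need about 1,240 per arm without continuity correction.

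**4. Patients randomised out of 771.** Per arm this is 771·(1 − f)/2.

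- f = one third: 257 per arm.
- f = 50% (assumed): 193 per arm, 183 evaluable. Power is 71% even at 36% against 24%.

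**The case against.** **The control risk is not known.** The 8.8% is a back-calculation. The 26% is given for TBI patients and the 65% for moderate-to-severe TBI, and the source study is not at hand to show that they describe one cohort. This stands, which is why a range is shown. At the source's relative risk, however, power is below 80% throughout that range, including at the centre's overall rate of 26%.

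**Power depends on the effect.** A reader might infer that the trial will give a null result whatever propranolol does, or that 80% power cannot exist here. The documents do not support that. At 8.8%, the odds ratio of 0.25 cited in the Introduction gives 88% power; at 13%, the 0.39 from the meta-analysis gives 82%. These effects were not the basis of the sample size, and the 0.25 comes from moderate-to-severe TBI. At 5% control risk neither reaches 80%.

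**The 65% should not be applied to all 771.** Doing so would leave 771 × 0.35/2 = 135 per arm. But that share describes moderate-to-severe TBI, and the Introduction reports a likely dose-response between myocardial injury and head-injury severity. Including mild cases should lower the positive share and leave more patients to randomise. The 135 is therefore not a documented expectation.

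**The link to 36% and 24% is not unique.** A pair such as 40% and 28% without continuity correction gives 243.4/0.95 = 256.3, also 257 after rounding up. The link rests instead on both sections citing the same study for the 12-point difference.

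**A target of 257 per group already implies 514 randomised.** True, but recruitment and the interim looks are counted on 771, so the two statements can diverge.

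**Conclusion.** The calculation is correct; the population behind its inputs is not the one randomised. The stated 80% power, and the Study rationale's claim of sufficient power, are unsupported for group 2 against group 3. On the derived 8.8% control risk and the source's relative effect, power is about 24%. It depends strongly on two quantities the protocol does not give for HsTnT-negative patients: their mortality and the effect expected in them. Including mild TBI should move mortality below the derived figure. The 8.8% assumes that the centre's three figures share one cohort; the conclusion that 80% power is unsupported does not need that assumption. Separately, 771 enrolled yields 257 per randomised arm only at a one-third positive share, which the article does not justify. The only calculation presented concerns mortality, so the claim about neurological outcomes has no stated basis either.

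**What to change.** - Restate the power and detectable difference for group 2 against group 3, over a range of HsTnT-negative 30-day mortality and a stated, justified set of effects, at the number expected to be randomised.
- Give the expected HsTnT-positive share. Then either count the recruitment target as HsTnT-negative patients randomised (257 per arm, 514 in all), or restate power for the number that 771 enrolled will yield.
- Withdraw or qualify the Study rationale's claim of sufficient power for mortality and neurological outcomes.

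The cost is revised wording and a less favourable stated power. The restatement needs no added patients. Choosing 514 randomised as the target could raise total enrolment above 771 if more than one third prove HsTnT-positive; keeping 771 and restating power avoids that.
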